Despite this volume of evidence, there remain several critical unresolved questions pertinent to sanctioned OPC implementation in the US. First, as noted in a recent systematic review, [13] the majority of OPC research has involved sites located in Canada, France and Australia, which differ substantially from the US context. Domestic research is urgently needed, particularly in the era of unprecedented overdose rates driven by the fentanyl crisis. [27, 28] Moreover, differences in local drug markets, racialized policing practices, healthcare policy, wrap-around services, and the types of OPC service delivery models adopted may modify the effectiveness of OPCs relative to other countries, and thus warrant additional study. Second, while studies of the unauthorized US site are promising, its clandestine nature limits its scope of operations (and thus its impact). [29] Hence, the impact of sanctioned OPCs (serving a much larger and more diverse client population) on neighborhood-level outcomes warrants further study. Third, there are few, if any, comparative investigations of different OPC models, [30] despite facilities varying substantially in structure, cost, service provision, and scope. [16] Fourth, while a small number of cost-effectiveness analyses have been conducted for operational OPCs in other countries and for hypothetical OPCs in the US, [24, 31] almost all of these studies rely on programmatic cost estimates from a single OPC in Vancouver, Canada, and focus on HIV infections averted as the main outcome.

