The Study Assessing the Effectiveness of Overdose Prevention Centers Through Evaluation Research (SAFER) aims to evaluate the effectiveness of the NYC and RI OPCs by conducting a parallel, multi-method, individual- and community-level evaluation of OPCs in NYC and RI in 2023–2027. By evaluating OPCs in these distinct contexts, SAFER intends to determine the generalizability of OPC effectiveness across diverse settings. The study aims include:*Identify individual health outcomes of OPC use* by investigating whether people who attend OPCs experience lower rates of fatal and non-fatal overdoses, drug-related health problems (e.g., skin & soft tissue infections), emergency department use, and a higher rate of initiating evidence-based treatment for substance use disorders, compared to people who use drugs and attend SSPs with no OPC.*Examine the community impact of OPCs* by determining whether census block groups surrounding OPCs experience a greater change in public health conditions (e.g., fatal and non-fatal overdoses), public disorder (e.g., drug-related litter, arrests, noise complaints), and acute economic conditions (e.g., property values) relative to a comparison set of census block groups unexposed to OPCs.*Investigate how operational contexts, program models, and operating procedures* shape how people who use drugs use OPCs and explore their impact on overdose vulnerability and other drug-related health outcomes, using qualitative and ethnographic methods.*Estimate OPC costs and potential cost savings to the healthcare and criminal justice systems associated with OPC use*, to support future estimation of longer-term cost and health outcomes.

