#### Neighborhood-level outcomes of interest

Since OPCs provide an environment where medical attention can be readily provided in the event of a drug overdose, we hypothesize that the opening of an OPC will be associated with significant decreases in the rate of drug overdose in neighborhoods where they are located. Using vital statistics records from the NYC Office of Chief Medical Examiner and the RI Office of State Medical Examiners, [59, 60] we will map drug overdose deaths based on the injury location on the death certificate. [61] We will define drug overdose deaths using underlying cause of death codes (X40-X44). [62] To measure non-fatal overdoses, we will use multiple data sources (Table 2), including Medicaid and EMS runs for suspected overdoses, and map these incidents based on their geographic coordinates (i.e., location of injury). [63]

Based on evaluations conducted in other settings, [11, 64–67] we also hypothesize that the opening of an OPC will be associated with improvements in measures of public safety, by bringing drug use indoors. Using publicly available arrest records from the NYC Police Department and the Providence Police Department, [68, 69] we will map the locations of drug-related offenses (e.g., possession of a controlled substance, criminal sale of a controlled substance) and other interpersonal crimes (e.g., assault, theft, larceny) as in prior work, [64] based on the location associated with each arrest.

Should the opening of an OPC be associated with improvements in public safety, we also hypothesize that the opening of an OPC will be associated with improvements in property values. Using publicly available data from the NYC Department of Finance and Providence Department of Finance, [70, 71] we will map historical property valuations and real estate sales to identify changes in assessed value and actual sale prices.

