#### Analyses

We propose to use causal inference techniques to evaluate the effectiveness of OPCs in the surrounding community. Specifically, using counterfactuals, we will consider the following causal question: among neighborhoods that implemented an OPC program, what is the estimated difference in overdose deaths (and other outcomes) between a hypothetical scenario where all neighborhoods adopted OPCs and a scenario where none did? To do so we will consider the average treatment effect among the treated (ATT) as the estimand of interest. The ATT considers how much better (or worse) the overdose deaths were for neighborhoods who actually opened an OPC compared to what their overdose deaths would have been if they had not opened it (counterfactual outcome). We will estimate the counterfactual expected number of drug overdose deaths using a linear regression controlling for potential sources of confounding (e.g., demographic characteristics, historical drug overdose rates, availability of harm reduction services). We will use the observed number of drug overdose deaths to estimate the expected overdose deaths for neighborhoods who actually opened an OPC. We will then take the difference between the two to compute an estimate of the ATT. We will use the sandwich estimator [72] to obtain its standard error and construct Wald 95% confidence intervals and Wald tests.

Our proposed methods are similar to the difference-in-difference method. [73] We will use a similar analysis for the measures of public safety. Informed by the intersectional risk environment framework, we will conduct a set of exploratory stratified analyses to identify whether and how the opening of OPCs may differentially impact public health and safety outcomes among people of different social groups.

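### Aim 2 tests its public safety hypothesis through arrest locations alone, so a change in policing near an OPC cannot be told apart from a change in offending

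*Protocol article*

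**What the plan says.** In Aim 2, under Neighborhood-level outcomes of interest, the article expects the opening of an OPC to bring "improvements in measures of public safety, by bringing drug use indoors". One data source is named for testing this: "Using publicly available arrest records from the NYC Police Department and the Providence Police Department". The events counted are "drug-related offenses (e.g., possession of a controlled substance, criminal sale of a controlled substance") and other crimes such as assault, theft and larceny. Each is mapped "based on the location associated with each arrest". The next paragraph of that section makes the property-value hypothesis conditional on an improvement in public safety.

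Under the Aim 2 Analyses heading the article says "We will use a similar analysis for the measures of public safety", that is, an ATT approach like the one for overdose deaths. The confounders it lists as examples are "e.g., demographic characteristics, historical drug overdose rates, availability of harm reduction services"; none concerns policing. The same section assumes that there is no time-dependent confounding and offers the E-value as a sensitivity analysis for unmeasured confounding.

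The study aims at the end of the Introduction describe the domain more broadly: "public disorder (e.g., drug-related litter, arrests, noise complaints").

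**The concern.** Arrest counts measure offending and police activity jointly. Possession and sale arrests depend most on discretion, because they usually follow from a police decision to stop or search and not from a victim's report. A sanctioned site to which people carry controlled substances could plausibly change nearby policing in either direction: fewer possession arrests so that clients can reach the site, or more patrols in response to community concern.

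The hypothesised mechanism makes this harder. Less drug use in public and less enforcement near the site both predict fewer possession arrests, so the chosen outcome cannot distinguish the effect the study hopes to find from a change in police practice. The Discussion says that at most three OPCs are evaluated, so one local policing decision would not average out over many sites.

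At stake is a public safety conclusion from a study that intends to inform legal and policy debate. A fall in drug arrests could be reported as improved safety, or a rise as harm, with offending unchanged.

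**Working it through.** The article states no sample size, arrest rate, effect size or enforcement change for this outcome, so there is no planned figure to reproduce. The check is an identity with assumed inputs.

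**Identity.** Let A be expected arrests, O offences and p the probability that an offence leads to an arrest in that place. Then A = O × p. Comparing the observed state with the state had no OPC opened, the ratios satisfy

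R_A = R_O × R_p.

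**Offending unchanged (R_O = 1.00), with R_p assumed:**

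| Assumed R_p near the OPC | R_A = 1.00 × R_p | Apparent change in arrests |
|---|---|---|
| 0.90 | 0.90 | 10% fall |
| 0.80 | 0.80 | 20% fall |
| 0.70 | 0.70 | 30% fall |
| 1.20 | 1.20 | 20% rise |

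**A true improvement can also be hidden.** With R_O = 0.80 and R_p = 1.20, R_A = 0.80 × 1.20 = 0.96. A true 20% fall in offending would appear as a 4% fall in arrests.

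**The two explanations are not identified.** R_A = 0.80 arises equally from R_O = 0.80 with R_p = 1.00 and from R_O = 1.00 with R_p = 0.80. Arrest data alone cannot choose between them.

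**Comparison areas.** Relative to comparison block groups, the ratio becomes (R_O treated / R_O comparison) × (R_p treated / R_p comparison). A proportional enforcement change common to both, for example one across the whole city, makes the second factor 1 and drops out. In the planned linear model, which works with differences, it drops out fully only where arrest levels are similar. A change specific to the OPC area remains.

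**Offence types.** One R_p should not be applied to every offence. The argument is strongest for possession and sale, and weaker for assault, theft and larceny, where a victim often starts the process.

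**Does the planned analysis deal with it?**
- The listed covariates include no policing measure. The list is only of examples, but adding post-opening enforcement would be no simple repair, because enforcement may itself result from the opening.
- The E-value asks how strong an unmeasured confounder must be to explain a result. A policing change that follows the opening is not a confounder, so the E-value does not address it.
- The assumption of no time-dependent confounding does not bear on what an arrest count measures.

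**The case against.** The strongest reply is that arrests are a declared outcome in their own right. The estimand is the effect of opening an OPC. If opening changes policing and therefore arrests, that is part of the true effect on arrests, and the ATT is not biased by it. This stands. The problem is one of construct: what the arrest result may be called, not whether it is estimated correctly.

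Four stronger readings are tempting, and the documents support none of them.

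- *Public disorder is measured only by arrests.* The study aims also name litter and noise complaints. The outcome section gives them no data source, but a journal article commonly leaves such detail to the full protocol, and silence does not show that they were dropped.
- *The distortion favours OPCs.* It can run either way, as the working shows.
- *Policing will change near OPCs and stay constant elsewhere.* The documents say neither. The Introduction does list "differences in local drug markets, racialized policing practices, healthcare policy", but as reasons why OPC effects may differ from those in other countries, not as something that shifts locally when a site opens.
- *The error enters the property-value estimates.* Those come from separate assessed values and sale prices. Only the condition attached to that hypothesis depends on the public safety result.

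It is also fair to say that the article cites prior work for mapping arrests, that complaint data are an imperfect proxy too, and that the study collects useful context: the Aim 1 survey asks about police stops, arrests and public syringe disposal, and Aim 3 includes fieldwork around the sites. This context can help interpretation, but none of it is an Aim 2 outcome and none separates enforcement from offending in the block-group analysis.

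**Conclusion.** The point holds as a matter of outcome choice and interpretation. The public safety hypothesis is operationalised through arrest locations, and nothing in the Aim 2 analysis separates enforcement from offending. Arrest results, especially for possession and sale, therefore cannot alone support a conclusion that public safety improved or worsened.

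The possible size equals the local proportional change in enforcement relative to comparison areas. The 10% to 30% falls and the 20% rise shown above are illustrations under assumed ratios, not estimates. They rest on unchanged offending and on an enforcement change specific to the OPC area, which is a risk and not a documented fact. The point warrants a change to the plan but does not invalidate the Aim 2 analysis of arrests as arrests.

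**What to change.** 1. Beside arrests, add reported-crime complaints (assault, theft, larceny) and resident service complaints for noise and litter as public safety and disorder outcomes. The study aims already name the last two. Use the same block groups and the same analysis.
2. Report possession and sale arrests separately, labelled as an enforcement outcome.
3. State in advance that improved public safety will not be concluded from drug arrests alone, and that the condition for the property-value hypothesis will not be treated as met on that basis.
4. Show the arrest and complaint series side by side, and discuss any divergence between them as possible evidence of changed policing or changed reporting.

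The cost is additional extracts from city agencies, whose availability in both cities must be confirmed, and little new analysis code. Complaint data have their own reporting behaviour, which could also shift around a contested site. That is why they should stand beside arrests and not replace them.

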#### Analyses

We propose to use causal inference techniques to evaluate the effectiveness of OPCs in the surrounding community. Specifically, using counterfactuals, we will consider the following causal question: among neighborhoods that implemented an OPC program, what is the estimated difference in overdose deaths (and other outcomes) between a hypothetical scenario where all neighborhoods adopted OPCs and a scenario where none did? To do so we will consider the average treatment effect among the treated (ATT) as the estimand of interest. The ATT considers how much better (or worse) the overdose deaths were for neighborhoods who actually opened an OPC compared to what their overdose deaths would have been if they had not opened it (counterfactual outcome). We will estimate the counterfactual expected number of drug overdose deaths using a linear regression controlling for potential sources of confounding (e.g., demographic characteristics, historical drug overdose rates, availability of harm reduction services). We will use the observed number of drug overdose deaths to estimate the expected overdose deaths for neighborhoods who actually opened an OPC. We will then take the difference between the two to compute an estimate of the ATT. We will use the sandwich estimator [72] to obtain its standard error and construct Wald 95% confidence intervals and Wald tests.

Our proposed methods are similar to the difference-in-difference method. [73] We will use a similar analysis for the measures of public safety. Informed by the intersectional risk environment framework, we will conduct a set of exploratory stratified analyses to identify whether and how the opening of OPCs may differentially impact public health and safety outcomes among people of different social groups.

Answering the proposed causal questions can be difficult for several reasons. First, we must assume that all confounders have been measured and accounted for. This is an untestable assumption that can be evaluated using sensitivity analyses, such as those based on the E-value. [74] Second, there may be the presence of time-varying confounders—confounders affected by previous treatments and influencing future ones. While techniques exist to control for this type of confounding, [75] practical positivity violations (also known as lack of overlap) prevent their deployment. Practical positivity violation occurs when the probability of a neighborhood with specific characteristics, as described by the considered confounders, opening an OPC is close to zero. This issue is inevitable given the low number of neighborhoods opening an OPC. To address this, we will assume there is no time-dependent confounding. Third, we will collect information over time within each neighborhood, necessitating consideration of possible clustering within neighborhoods over time. While clustering methods could be used, they might result in under-coverage if the analysis only considers a few OPCs (only a few neighborhoods are "treated"). [76, 77] As previously mentioned, we will use standard sandwich estimators without correction for clustering. Finally, to obtain an unbiased estimate of the ATT, we need to assume that the linear regression model used to estimate the counterfactual expected outcomes is correct. This is another untestable assumption that could be mitigated by using more flexible methods, such as machine learning techniques. While these techniques can learn complex data patterns, they cannot be used due to positivity issues and the limited number of observed data. Therefore, we assume that the parametric linear regression model used is correct.

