### Aim 1: Individual health and treatment outcomes associated with OPC use among PWUD

#### Study design

While a randomized controlled trial (RCT) would be the gold standard for OPC evaluation, community and political factors that drive the timing of OPC service openings make randomization unfeasible, and RCTs of OPCs have previously been deemed unethical due to a lack of equipoise. [35] Hence, we use a quasi-experimental, pre-/post-intervention design with a comparison group, [36] to test whether individuals who use an OPC experience greater changes in the outcomes of interest than individuals who do not use an OPC. We recruit participants from two types of organizations that serve similar populations, facilitating group comparability by level of OPC use: (1) harm reduction organizations that provide OPC services (two sites in NYC) or plan to provide OPC services (one site in RI); and (2) a comparison set of SSPs with no plans to open an OPC (five organizations in NYC and three in RI). The target sample is 250 in each arm per jurisdiction, so that we recruit 500 participants in NYC and 500 in RI (N = 1000 total). Target numbers per site are proportional to the client population served by each organization. We collect pre- and post-OPC data from all study participants, including administrative health records and survey data, as described below.

We use venue-based recruitment for two reasons. First, this ensures that all groups represent a comparable underlying population of individuals already connected to a harm reduction service provider. Second, this permits us to compare populations that receive harm reduction services (e.g., syringe exchange, naloxone), so we can isolate the effect of OPC use on outcomes.

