While our proposed study has the potential to make lasting contributions to our understanding of the impact of OPCs on the health of PWUD and local communities, it also poses some limitations. First, the political and ethical constraints on randomization limit causal inference. However, we propose several approaches to address time-dependent confounding in Aim 1, and the lack of a counterfactual comparison neighborhood in Aim 2. Second, the limited number of OPCs we evaluate (up to three OPCs across the two jurisdictions) limits our ability to make quantitative inferences about the impact of different models of OPC service delivery. However, we will explore this in our qualitative analysis (Aim 3), with the intent of quantifying differences in outcomes across service models in future research across a wider spectrum of OPCs. Third, loss to follow-up may constrain our ability to evaluate long-term outcomes associated with OPC use. However, our experience with longitudinal follow-up of similar populations, an extensive plan for cohort retention, and plans to complement survey data with administrative data, reduce this concern.

Our study leverages a multi-site design to provide generalizable insights about the effectiveness of OPCs. We will consider the extent to which the effectiveness of OPCs varies by the type of jurisdiction (NYC, RI), and will generate insights about the types of operational contexts, program models, and operating procedures which contribute to the most promising outcomes. Finally, we will collect rich data on the costs and savings associated with the implementation of OPCs. Policymakers and practitioners considering opening OPCs in other jurisdictions will be able to use our findings as an evidence base to inform the types of approaches that could work best in their own context.

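### Aim 2 rejects clustering methods for fear of under-coverage, but the uncorrected sandwich it adopts also under-covers unless residual correlation within neighbourhoods is near zero

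*Protocol article*

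**What the plan says.** In Aim 2, Analyses, the estimand is the average treatment effect among the treated: observed outcomes in OPC neighbourhoods minus a counterfactual predicted by linear regression, with historical overdose rates among the covariates. On inference the article says: "We will use the sandwich estimator [72] to obtain its standard error and construct Wald 95% confidence intervals and Wald tests".

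The same section raises dependence: "we will collect information over time within each neighborhood, necessitating consideration of possible clustering within neighborhoods over time". It sets clustering methods aside because "they might result in under-coverage if the analysis only considers a few OPCs", and concludes: "As previously mentioned, we will use standard sandwich estimators without correction for clustering".

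The Discussion puts the number of treated locations at "up to three OPCs across the two jurisdictions". The Aim 1 study design gives the split: "two sites in NYC) or plan to provide OPC services (one site in RI". Under the heading on defining the neighbourhood around an OPC, each treated area is made up of census block groups around one site.

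The article describes no small-sample, placebo or aggregated inference for Aim 2. The one sensitivity analysis it names, the E-value, addresses unmeasured confounding and not the standard error.

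**The concern.** The stated worry is under-coverage, and the response is to make no correction. An uncorrected sandwich treats the records entering the regression as independent once covariates are fitted. If records from one neighbourhood share a residual component, such as a local change in drug supply, policing or reporting, the standard error is too small. Block groups around one OPC share that site and its local shocks, so they do not add independent treated units. The normal reference is a second weakness when the treated side rests on two or three locations.

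These tests carry the Aim 2 conclusion on overdose deaths, and the article extends a similar analysis to public safety. A local shock near one site could be reported as a significant benefit or harm of OPCs, in a study that means to inform legal and policy debate.

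**Working it through.** **No figure to reproduce.** The article states no power, standard error or coverage for Aim 2. The only benchmark is the nominal 95% interval, that is, 5% error.

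**Inputs from the article:** at most three OPCs; repeated records within neighbourhoods; linear counterfactual model with historical rates as a covariate; sandwich standard error; Wald test; no clustering correction.

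**Assumptions, because the article gives no values:** 60 comparison neighbourhoods; 1, 8 or 24 post-opening records each; in one variant 8 block groups per neighbourhood; residual correlation from 0 upwards.

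**Analytic check, one series per neighbourhood.** With m equally correlated records per treated neighbourhood, the variance is inflated by DE = 1 + (m - 1)ρ, and the actual error of the nominal 5% test is 2[1 - Φ(1.96/√DE)]. For m = 24:

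- ρ = 0.05: DE = 1 + 23 × 0.05 = 2.15, error 18.1%
- ρ = 0.10: DE = 1 + 23 × 0.10 = 3.30, error 28.1%

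**Analytic check, 8 block groups by 8 periods.** Each record has 7 others in its own block group and 7 × 8 = 56 in the neighbourhood's other block groups, so DE = 1 + 7(ICC_n + ICC_b) + 56 ICC_n, where n is neighbourhood and b is block group.

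| ICC_n | ICC_b | DE | Coverage 2Φ(1.96/√DE) - 1 |
|---|---|---|---|
| 0.01 | 0.05 | 1.98 | 84% |
| 0.02 | 0.05 | 2.61 | 78% |
| 0.05 | 0.10 | 4.85 | 63% |
| 0.10 | 0.10 | 8.00 | 51% |

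**Simulation of the stated estimator under no effect.** The counterfactual model is fitted on comparison neighbourhoods with the historical mean as covariate. The effect is the treated mean minus the prediction, with a sandwich error computed record by record and a normal Wald test. There are 3 treated and 60 comparison neighbourhoods, with 3,000 runs per setting (1,500 with block groups).

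| Setting | Residual correlation | Uncorrected: type I error | Mean SE / true SD | Cluster-robust, normal reference: type I error |
|---|---|---|---|---|
| 24 records | 0 | 6.2% | 0.98 | 21.3% |
| 24 records | 0.02 | 11.4% | 0.80 | 21.9% |
| 24 records | 0.05 | 18.7% | 0.67 | 22.3% |
| 24 records | 0.10 | 28.0% | 0.54 | 21.0% |
| 8 records | 0 | 7.1% | 0.96 | 22.0% |
| 8 records | 0.10 | 16.8% | 0.71 | 21.2% |
| 1 record | none | 21.2% | 0.76 | 21.2% |
| 8 block groups × 8 periods | ICC_n 0.02, ICC_b 0 | 20.5% | 0.64 | 23.1% |
| 8 block groups × 8 periods | ICC_n 0.05, ICC_b 0 | 35.8% | 0.46 | 23.3% |
| 8 block groups × 8 periods | ICC_n 0.10, ICC_b 0.10 | 48.8% | 0.34 | 21.2% |

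The one-record row has no repeated records to correlate, so its excess error comes purely from having three treated units.

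**Alternatives, three treated neighbourhoods.** Cluster-robust errors with a t reference on 3 - 1 = 2 degrees of freedom gave about 1.4-2.3% error. Placebo reassignment over comparison neighbourhoods gave about 4-7% (600 runs per setting), with exchangeable neighbourhoods simulated.

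**The case against.** - **The size is not in the documents.** A reader might infer that the intervals are certainly far too narrow and false positives common. The documents do not support that as a fact: correlation, periods and comparison areas are all unstated, and at zero residual correlation with repeated records the error is close to nominal. This stands, and the conclusion is conditional for that reason.
- **The unit of analysis is not fixed.** The article does not specify a regression on block-group-by-period records, and it speaks of neighbourhoods. This stands too. The rule still fails with one record per neighbourhood, though from too few treated units and not from ignored clustering.
- **Covariates may absorb correlation.** Historical rates are adjusted for, so only residual correlation matters. This is true, but absorption cannot be assumed. Where areas differ persistently and the historical mean measures that level with error, the simulation with 24 records gave 16% error even with no added correlation, and 27% at 0.05.
- **The worry about clustering methods is sound.** The ordinary cluster-robust Wald test gave about 19-23% error with three treated units, and it is worse than the uncorrected test when correlation is low. Simply switching on a cluster option would not repair the plan. It does not follow that every cluster-based method is invalid, because the t reference on 2 degrees of freedom does not under-cover here.
- **Under-coverage need not grow without limit.** If correlation decays over time as AR(1) with parameter 0.4, inflation from adding periods is bounded near (1 + 0.4)/(1 - 0.4) = 2.33, or about 80% coverage. Unlimited growth needs correlation that does not decay.
- **Placebo inference has its own assumption.** The article itself says that some neighbourhood profiles have almost no chance of an OPC, so exchangeability is doubtful, most of all in RI.
- **Property values.** The article names public safety for the similar analysis. Property values are covered at most by its general reference to other outcomes.

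**Conclusion.** The stated reason does not justify the stated rule. Avoiding clustering methods does not avoid under-coverage. It replaces one source with an assumption of zero residual correlation and keeps the normal reference for at most three treated locations.

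Under the assumptions listed, type I error against a nominal 5% is about 6-7% at zero residual correlation with repeated records, 11-28% at correlation 0.02-0.10 with 24 records, 20-49% with 8 block groups by 8 periods at neighbourhood ICC 0.02-0.10 (the upper end also has a block-group ICC of 0.10), and about 21% with one record per neighbourhood. The direction is well supported. The exact size cannot be known from the article. The authors disclose the choice openly, so this is a badly fixed inference rule and not a contradiction or an omission.

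**What to change.** Delete the sentence adopting uncorrected sandwich errors, revise the Wald statement before it to match, and take the OPC neighbourhood as the unit of inference. Either of these would serve:

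1. **Placebo (permutation) inference within jurisdiction.** Compute the same effect for comparable non-OPC areas and take p-values and test-inverted intervals from that distribution. State that this assumes the areas are exchangeable.
2. **Cluster-robust errors with a t reference on (treated clusters - 1) degrees of freedom**, for the pooled analysis. This is conservative with three treated.

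A stand-alone RI test has one treated area, so the smallest placebo p-value is 1/(k + 1) with k placebo areas. Reaching 0.05 needs k of at least 19, since 1/(19 + 1) = 0.05. If that many comparable areas are not available, report RI descriptively. The article does not show that they are.

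The cost is revised analysis wording and some computing, largely on the same area-level data, with no new participants. The downside is wider intervals and less favourable p-values.
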